#### Primary outcomes

*Biochemical assessment I*: *Fasting blood samples*. Blood collection will be performed in a seated position from the antecubital vein, at rest after a 12-hours overnight fast, and the blood samples will be aliquoted into kEDTA and serum tubes. The participants will be instructed to avoid extreme physical efforts 24 hours before the blood collection. Determination of blood counts will be done immediately after the blood collection, using an automated Coulter Ac•T diff Hematology Analyzer (Beckman Coulter^®^, Inc, USA). Biological samples will be centrifuged at 1500xg for 10-min and plasma and serum samples will be frozen at -80°Celsus (C) for posterior analysis. The levels of insulin, glucose, glycated haemoglobin (HbA1c), total cholesterol, low-density lipoprotein cholesterol (LDL-C), HDL-C, triglycerides, cytokines IL-1β, IL-1ra, IL-6, IL-10, transforming growth factor beta 1 (TGF-β), TNF-α, adiponectin and leptin will be analysed. Fasting glucose, triglycerides and cholesterol levels will be determined by standard enzymatic assays (ABX Pentra, Germany). Insulin, leptin and adiponectin will be analysed by ELISA (R&D Systems, UK). The Homeostatic model assessment (HOMA-IR) will be calculated using the Matthews formula [65]:

$$HOMA-IR=\frac{fasting\;glucose\;[mmol/L]\;x\;fasting\;insulin\;[\mu U/l]}{22.5}$$

Inflammatory cytokines will be analysed by ELISA kits (Thermofisher, UK) according to the manufacturer instructions. All blood collections for the biomarker analysis will be performed in the morning (between 07:30h – 10:30h) by a registered nurse.

*Biochemical assessment II*: *Saliva samples*. Saliva will be collected through a gold standardized method for biological assays—passive drool—which requires participants to “expel” saliva (let the saliva drop) into polypropylene tubes [66]. The participants will be comfortably seated with their head slightly lowered, allowing spontaneous saliva flow to accumulate in their mouth [67]. Before saliva collection, the participants will be instructed to rinse their mouth for 60 seconds with water to remove any food residues and then wait at least 10 minutes [67, 68] before saliva collection. Moreover, according to procedures in other studies, the participants will be required to avoid vigorous physical exercise 24h before the collection, alcohol for 12 hours, brush teeth or eat a major meal for 60 minutes, and foods with high sugar, acidity, or caffeine immediately before sample collection [67, 68]. After collection, saliva samples will be stored frozen at −20°C until assayed. The saliva samples will be subject to a single freeze-thaw cycle. On the day of the assay, samples will be centrifuged to remove particulate matter, and the salivary levels of cortisol (s-COR), α-amylase (s-AA), immunoglobulin A (s-IgA), and Lysozyme (s-Lys) will be analyzed by commercial kits. S-COR, s-IgA, and s-Lys will be analyzed by ELISA (Salimetrics, USA) and s-AA by a kinetic reaction assay (Salimetrics, USA), according to the manufacturer instructions. All saliva collections for biomarker analysis will always occurred at the same time in the morning to minimize circadian effects (between 09:30h – 10h30).

*Brachial blood pressure*. The right and left brachial systolic blood pressure (SBP) and diastolic blood pressure (DBP) will be measure using an automated oscillometric cuff (OMRON, HEM 907, Japan). The participant will be comfortably seated, with the legs uncrossed and the back and arm supported, for 3–5 minutes without speaking and/or moving before recording the first measure [69, 70]. Two readings will be taken at intervals of at least 1–2 minutes and the average of those readings will be recorded as the participant’s BP. However, if the values deviate by ≥ 5 mmHg, a third measurement will be performed, and the average of these multiple readings will be used [69, 70]. The participants must avoid caffeine, physical exercise, and smoking for at least 30 minutes prior to measurement [69]. The brachial BP will be assessed in the morning (between 09:00h – 12:00h) and will be performed by a doctor.

*Lung function*. Spirometry will be conducted using the Spiropalm 6MWT (Cosmed, Italy) Spirometer. Participants will perform a maximal inspiratory and expiratory maneuver to achieve the Forced Vital Capacity (FVC), Forced Expiratory Volume in 1 second (FEV_1_), and Peak Expiratory Flow (PEF). Participants’ data will be classified to indicate repeatability. In this sense, the participants will have to complete at least three acceptable FVC maneuvers to be included in the analysis (i.e., the difference between the best two FEV_1_ and FVC values must be within 150 mL) [71, 72]. The best FEV_1_ and best FVC measures of the participants will be recorded and used for data analysis, according to procedures adopted in other studies [20, 21]. Predicted FEV_1_ (FEV_1_% pred), predicted FVC (FVC% pred), and predicted PFE (PFE% pred) will be calculated based on age, stature, ethnicity, and sex using the formulas developed by the Global Lung Function Initiative [73]. The lung function assessment will occur in the morning (between 09:00h – 12:00h) and will be performed by a doctor.

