
Unfortunately, the high methodological confounds of some of the previous studies and knowledge gaps lead to little evidence regarding the effectiveness of CT to improve the biochemical and immune markers of metabolic disease, lung function, quality of life, and stress in sedentary adult office workers. So, new studies are required to improve the quality of evidence on this topic. This trial aims to analyse the effects of a 16-week CT program on metabolic disease risk markers, including inflammatory cytokine profile, markers of IR (fasting glucose and insulin levels, HOMA-IR), leptin and adiponectin levels (as surrogate markers of adipose tissue dysfunction), lung function, salivary stress hormones and subjective quality of life (primary outcomes), as well as body composition and physical fitness (secondary outcomes), in sedentary middle-aged office workers of both genders. Furthermore, we aimed to assess the associations between the changes promoted by the exercise intervention and the different variables studied.

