### Data analysis

Data analyses will be performed using SPSS Statistics version 25.0 (SPSS Inc., IBM Company, Chicago, Illinois, USA). Descriptive statistics (mean ± SD) will be performed for all variables in the analysis. The assumption of normality will be tested using histograms, normal probability plots and Shapiro-Wilk test. Chi-squared test will be performed to analyse sex proportions between groups. Assuming data normality, a two-way analysis of variance (ANOVA) for repeated measures will be applied for intra- and inter-group comparisons. In absence of normality, non-parametric Kruskall-Wallis test will be used. Bonferroni’s *post hoc* test will be performed if significant differences exist (alpha level set at 0.05). The magnitude of the global effect size will be calculated using Cohen’s effect size [104]. The Cohen’s d effect size is categorized according to the following criteria: *d* = < 0.20 (small), 0.21–0.79 (medium) and > 0.80 (large) [104]. The bivariate associations between the changes promoted by the exercise program and the different variables studied will be assessed by Spearman’s rank and Pearson’s coefficients. The strength of the associations will be classified as follows [105]: very high (0.90 < r < 1.00); high (0.70 < r < 0.90); moderate (0.50 < r < 0.70); low (0.30 < r < 0.50); little (0.10 < r < 0.30). Significance level set at *p* ≤ 0.05.

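### The printed HOMA-IR formula gives insulin per litre where the constant 22.5 needs it per millilitre; taken literally, values come out 1000 times too large, though no planned test is affected

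*Protocol article*

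**What the plan says.** The aims at the end of the Introduction place "markers of IR (fasting glucose and insulin levels, HOMA-IR" among the measures designated as primary outcomes. Under Primary outcomes, in the part on fasting blood samples, the protocol article states that "The Homeostatic model assessment (HOMA-IR) will be calculated using the Matthews formula" and then displays the equation. In the source notation of that equation, the glucose term reads "fasting\;glucose\;[mmol/L", and the insulin term with the divisor reads "fasting\;insulin\;[\mu U/l]}{22.5". The rule as printed is therefore glucose in mmol/L, times insulin in µU/L, divided by 22.5.

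The same part says that "Insulin, leptin and adiponectin will be analysed by ELISA (R&D Systems, UK", without giving the unit in which the assay reports insulin. The bracket in the equation is the only insulin unit in the article. No HOMA-IR reference value, cut-off or conversion appears anywhere else. For the analysis, the Data analysis section plans means and SDs for all variables and says that "a two-way analysis of variance (ANOVA) for repeated measures will be applied for intra- and inter-group comparisons".

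**The concern.** The equation is a stated derivation rule for a primary-outcome marker, not background text, and its insulin unit does not fit its constant. The divisor 22.5 scales the index so that a reference person scores about 1, and with glucose in mmol/L it does so only when insulin is in µU/mL. An analyst who converted insulin to the printed unit before applying the equation would report HOMA-IR levels and absolute changes a thousandfold too large. Those figures could not be set beside results from other studies until they were rescaled. A reader who copied the equation into another protocol would copy the error too.

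**Working it through.** **Inputs from the protocol article:** glucose in mmol/L; insulin in µU/L; divisor 22.5; the named method (Matthews formula). The article states no numerical HOMA-IR value, so there is no figure of its own to reproduce; the check is one of units.

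**Inputs assumed, not in the article:** fasting glucose 4.5 to 6 mmol/L and fasting insulin 3 to 20 µU/mL, for illustration only. The factor found in step 2 does not depend on them.

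**Step 1: which unit fits 22.5.** The constant is the product of reference values 4.5 mmol/L and 5 µU/mL:

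4.5 × 5 = 22.5, so HOMA-IR = 22.5 / 22.5 = 1.0

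The same person with insulin in µU/L (5 µU/mL = 5,000 µU/L) gives

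4.5 × 5,000 / 22.5 = 1,000

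A reading in pmol/L does not fit either. Taking about 6 pmol/L per µU/mL (an assumption), insulin of 8 µU/mL is 48 pmol/L, and at glucose 5 mmol/L the index is 5 × 48 / 22.5 = 10.7, against 5 × 8 / 22.5 = 1.78 in µU/mL.

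**Step 2: size of the error.** Because 1 µU/mL = 1 mU/L = 1000 µU/L, the ratio of the literal to the intended value is 1000 for every input:

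| Glucose (mmol/L) | Insulin (µU/mL) | Insulin in µU/mL | Insulin in µU/L, as printed |
|---|---|---|---|
| 4.5 | 3 | 0.60 | 600 |
| 5 | 5 | 1.11 | 1,111 |
| 5 | 10 | 2.22 | 2,222 |
| 6 | 20 | 5.33 | 5,333 |

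**Step 3: the reverse check.** For the printed equation to give 1 at glucose 5 mmol/L, insulin must be 22.5 / 5 = 4.5 µU/L, which is 0.0045 µU/mL. That lies far below the assumed fasting range of 3 to 20 µU/mL.

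**Step 4: effect on the planned analyses.** Let every value be multiplied by c = 1000.

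- ANOVA: every mean square is multiplied by c², so each F ratio and its p-value are unchanged.
- Cohen's d: the mean difference and the SD are both multiplied by c, so d is unchanged.
- Kruskal-Wallis and Spearman: ranks are unchanged.
- Pearson: the covariance and one SD are both multiplied by c, so r is unchanged.

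A simulated data set with 20 per group agreed. Before and after multiplication, the two-group t statistic was 0.056 (p = 0.955), Cohen's d 0.018, the Kruskal-Wallis p-value 0.358 and the Pearson coefficient −0.281. Only means, SDs and absolute differences change, each by the factor 1000.

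**The case against.** The strongest reply is that this is a slip in one unit label and not a wrong method. The article names the formula; the structure, the glucose unit and the constant all fit it; only the volume in the insulin unit is off. For harm to follow, an analyst would have to convert insulin to µU/L and then accept indices above 1,000. That is unlikely, and it is why the severity is low. The label is still wrong, and nothing else in the article corrects it.

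A second reply is that the article contains no figure showing which unit belongs with 22.5, so this is not a contradiction between two of its statements. That is fair. The point rests on the standard definition of an index that the article names, plus unit conversion.

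Three stronger readings are tempting, and the article supports none of them:

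- A reader might infer that the insulin-resistance result would be invalid. The planned tests, effect sizes and correlations do not change with scale, no cut-off or eligibility rule uses HOMA-IR, the sample size section does not refer to it, and fasting glucose and insulin are listed as markers in their own right.
- A reader might infer that the values could never be compared or pooled with others. A known constant factor is undone by dividing by 1000.
- A reader might infer an error in handling the ELISA output. The article states no output unit, so none can be shown, and such laboratory detail is commonly left to the full protocol.

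**Conclusion.** The point holds as an error in a stated formula, of low severity. As printed, the insulin unit is incompatible with the divisor 22.5, and literal use makes every HOMA-IR value, mean, SD and absolute between-group difference exactly 1000 times too large. The factor is exact and needs no assumption about the participants; the illustrative indices in the working depend on the assumed glucose and insulin values. The conclusion assumes that the standard form of the named index is intended. The cause is most likely typographical, and the consequence is confined to descriptive levels and absolute changes.

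**What to change.** In the displayed equation under Primary outcomes, change the insulin unit from µU/L to µU/mL (equivalently mU/L), leave the glucose unit and the divisor 22.5 as they are, and derive HOMA-IR from insulin expressed in that unit. The correction alters one unit label. It touches no design element, sample size, test or data collection, and costs nothing beyond the erratum or amendment that records it.

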### Exercise intervention

The exercise program will be conducted following the American College of Sports Medicine (ACSM) recommendations [29, 55]. The exercise sessions will occur 3 times/week (i.e., Monday, Wednesday, and Friday) during approximately 75 min/session over 16 weeks (achieving 225 min/week, meeting public health guidelines for middle-aged adults), in an enclosed gymnastic pavilion. All exercise sessions will be conducted and supervised by two instructors who graduated in Sport Sciences with wide experience in the area. The two instructors are also responsible for encouraging participants to complete the exercise sessions/program, provide feedback, and assure the correction and safety of exercise execution. Before starting the exercise program, subjects will be submitted to estimated maximal dynamic strength tests aiming at setting their workload (i.e., 10 repetitions maximum (RM) protocol) [56].

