### Outcome measures

This trial includes a screening and baseline assessment period of 20 days (four visits), a 16-week CT program period, and a mid-testing and post-testing period of 3 (one visit) and 10 days (two visits), respectively. On the first visit, subjects will sign the informed consent form and will complete additional screening measures. Subjects that meet all eligibility criteria will be enrolled and complete a set of outcome measures over visits 2 and 3. After the baseline assessments, subjects will be randomly assigned to either control or experimental group, and the participants of the experimental group will carry out the evaluations of 10RM (Visit 4). The exercise sessions will be performed over 16-weeks on a single site and supervised by two instructors. Baseline assessments will be repeated after 8 weeks (mid-testing, visit 5) and upon completion of the intervention (visits 6 and 7). Importantly, we will consider the phase of the menstrual cycle in non-menopausal women (i.e., menstrual phase, follicular phase, ovulation phase and luteal phase), taking baseline and follow-up evaluations at the same time of the cycle. A timetable of the enrolment, intervention and assessments are presented in Table 3.

**Table 3 pone.0263455.t003:** Schedule of enrolment, interventions, and assessments.

	STUDY PERIOD							
	Baseline				Intervention	Follow-ups		
Timepoint	Visit 1^a^	Visit 2^a^	Visit 3^a^	Visit 4^a^	Sessions 1–48^b^	Visit 5^c^	Visit 6^d^	Visit 7^d^
Day number	-20 to -15	-15 to -10	-10 to -5	-5 to -1	1 to 112	56 to 58	113 to 118	118 to 123

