**ASSESSMENTS**								
Fasting blood samples		x					x	
Saliva samples		x					x	
Body composition			x			x		x
Physical fitness			x			x		x
Lung function (Spirometry)			x			x		x
Subjective quality of life			x			x		x
Systolic and diastolic blood pressure	x		x			x		x
Assessment of dietary intake			x					x
Accelerometry		x					x	
**RANDOMIZATION**				x				
Maximal dynamic strength to estimated 1RM				x		x		

^a^ Screen and baseline assessments will be completed within 20 days;

^b^ The exercise sessions will be performed 3 times/week (i.e., Monday, Wednesday, and Friday) over 16 weeks;

^c^ This study includes an intermediate assessment, which will be carried out in the eighth week of intervention;

^d^ Post-testing assessments will be done within 10 days of the last exercise session.

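### At mid-test only, the 30-minute exercise rule lets blood pressure be read soon after exertion that only the training arm undergoes

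*Protocol article*

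**What the plan says.** All references are to the protocol article.

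- **Blood pressure (Primary outcomes).** The preparation rule is "The participants must avoid caffeine, physical exercise, and smoking for at least 30 minutes prior to measurement". On timing: "The brachial BP will be assessed in the morning (between 09:00h – 12:00h) and will be performed by a doctor".
- **Other samples in the same section.** For blood: "The participants will be instructed to avoid extreme physical efforts 24 hours before the blood collection". For saliva: "the participants will be required to avoid vigorous physical exercise 24h before the collection".
- **Training days (Exercise intervention).** "The exercise sessions will occur 3 times/week (i.e., Monday, Wednesday, and Friday"), over 16 weeks. Table 3 runs the sessions from day 1 to day 112.
- **Visits (Outcome measures).** The text gives "a mid-testing and post-testing period of 3 (one visit) and 10 days (two visits), respectively". Table 3 puts Visit 5 at days 56 to 58 and Visit 7 at days 118 to 123.
- **Table 3 rows.** "Systolic and diastolic blood pressure" is marked at Visits 1, 3, 5 and 7. The row "Maximal dynamic strength to estimated 1RM x x" is marked at Visits 4 and 5. Blood and saliva are not taken at Visit 5.
- **10RM test (Supportive measures).** It is done by the combined-training group only, on six free-weight exercises, also between 09:00 and 12:00.
- **Control group (Randomization).** Controls keep their usual habits and join no exercise programme.

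**The concern.** Visit 5 is the only blood pressure assessment held while training continues, and the only one that shares a visit with the 10RM test. At baseline the readings (Visits 1 and 3) come before the 10RM test (Visit 4). The mid-test exposure is therefore new since baseline and confined to one arm.

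If exercise shifts blood pressure for some hours, the shift would appear at mid-test in trainees and not in controls. The planned two-way repeated-measures ANOVA cannot separate it from an adaptation to eight weeks of training. Randomisation and blinded assessors do not remove it, because it arises after allocation and from the state of the participant, not from the observer. If the shift is a lowering, it would look like benefit.

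**Working it through.** **1. The plan's own calendar.** 3 sessions x 16 weeks = 48 sessions, and 16 x 7 = 112 days. Both match the article.

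**2. Does days 56 to 58 always include a training day?** Day 57 = 8 x 7 + 1, so it falls on the same weekday as day 1. The last column below lists window days whose preceding day had no session.

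| Day 1 | Days 56, 57, 58 | Session days | Days after a session-free day |
|---|---|---|---|
| Mon | Sun, Mon, Tue | Mon | Sun, Mon |
| Tue | Mon, Tue, Wed | Mon, Wed | Mon, Wed |
| Wed | Tue, Wed, Thu | Wed | Wed |
| Thu | Wed, Thu, Fri | Wed, Fri | Wed, Fri |
| Fri | Thu, Fri, Sat | Fri | Fri |
| Sat | Fri, Sat, Sun | Fri | Fri, Sun |
| Sun | Sat, Sun, Mon | Mon | Sun, Mon |

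A session day falls in the window for every start.

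**3. When would a session precede the reading by less than 24 hours?** Take a Monday start. On day 57 the session must end by 11:30 (12:00 minus 30 minutes). On day 58, a reading at the earliest slot, 09:00, is within 24 hours only if the day-57 session ended after 09:00; later slots need a later end. Both days are exposed only if sessions end between about 09:00 and 11:30. With afternoon or evening sessions only day 58 is exposed. The article does not state session times.

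**4. The 10RM route.** This needs no assumption about session times. Test and reading share one visit and one three-hour slot. Taking the stated set numbers per exercise, the test is 6 x (2 warm-up + 3 to 5 test sets) = 30 to 42 sets. A reading 30 minutes afterwards satisfies the rule.

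**5. The other time points.** Readings at Visits 1 and 3 precede Visit 4 and all training. With a Monday start the last session is day 15 x 7 + 5 = 110, so Visit 7 opens 118 - 110 = 8 days later. Over all seven starts the gap is 6 to 8 days.

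**6. Size.** Shift in the mid-test arm contrast = share of trainees read in the exposed state x acute drop. The documents give neither input. Assuming a drop of 3 to 8 mmHg systolic:

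- share 0: 0 mmHg
- share 0.5: 0.5 x 3 = 1.5 to 0.5 x 8 = 4 mmHg
- share 1: 3 to 8 mmHg

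**7. What a shift would do to a test.** As an illustration, take a two-sided 5% comparison at mid-test with 20 per arm and no true training effect. Let s be the mean shift in SDs of the change. The chance of significance is Phi(s/sqrt(2/20) - 1.96) + Phi(-s/sqrt(2/20) - 1.96). For s = 0.10, 0.25, 0.50 and 0.75 this gives about 6%, 12%, 35% and 66%, against a nominal 5%. The article states no blood pressure SD, so the mmHg figures in step 6 cannot be placed on this scale.

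**The case against.** **Test order and session times are operational detail that an article leaves to the full protocol.** This stands as far as it goes: their absence is no fault. The point rests on what the article does fix, namely a 30-minute interval that both exposures satisfy.

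**The mid-test is meant to come before the week-9 change of load.** A Table 3 footnote puts it in the eighth week, and the 10RM test is there to update prescriptions. With a Monday start, session 25 (8 x 3 + 1) opens week 9 on day 57. This makes a reading after session 25 less likely, but the stated window runs to day 58, and the 10RM route is untouched.

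**The documents give no direction or size for the acute effect.** This stands. The cool-down text under Exercise intervention says only that heart rate and blood pressure need to recover.

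**Blood pressure carries modest weight.** It sits under Primary outcomes but is not named in the aims of the Abstract or Introduction. This also stands.

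Stronger readings that a reader might infer, and that the documents do not support:

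- *The 16-week result is biased.* Visit 7 is at least 6 days after the last session, and no 10RM test is scheduled there.
- *The 30-minute and 24-hour rules contradict each other.* They govern different measurements. The 24-hour rules bar extreme effort (blood) or vigorous exercise (saliva), not all exercise.
- *Two of the three mid-test days are always exposed.* That depends on unstated session times (step 3).
- *Step-test and bioimpedance results are biased towards benefit as well.* Nothing in the documents shows a direction or size for either, and the step test itself is done in both arms.

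**Conclusion.** The point holds for Visit 5 only. The 30-minute rule permits a one-arm exposure to acute exercise before a measurement listed as primary, through the same-visit 10RM test or a session within the previous 24 hours. Its presence in the data is possible rather than certain. The size is zero if blood pressure is scheduled first and before any session; the 1.5 to 4 mmHg figure rests wholly on the assumed 3 to 8 mmHg drop and the assumed half of trainees exposed. The comparison of baseline with 16 weeks, which answers the trial's stated aim, is not affected. It is still worth correcting, because an acute shift could not be separated from a training effect once the data are collected.

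**What to change.** For Visit 5 only:

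1. Require 24 hours without a training session or other vigorous exercise, the 10RM test included, before blood pressure. This matches the interval already used for saliva (vigorous exercise) and blood (extreme effort).
2. Take blood pressure before any exertion test, and put the 10RM test last in the visit or on another day.
3. Book trainees on a morning before that day's session that follows a day without training. With a Monday start this is day 56, or day 57 before the session.

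The change is to wording and booking; the exercise programme stays as it is. With a Monday start it costs one of the three window days. By the table in the working, a Wednesday or Friday start would leave only one usable day, so the window might then need to be a day or two wider. No change is needed at Visits 3 and 7.
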